### Outcomes

2.9

#### Feasibility

2.9.1

The feasibility of TQF and trial design will be explored as the primary outcome. The key domains for the assessment include recruitment, intervention protocol, outcome assessments, and data collection methods. The eligibility, recruitment, retention, and completion rates will be investigated at the end of the pilot trial:

1) Eligibility rate: the percentage of eligible participants over the number of screened participants;2) Recruitment rate: the percentage of recruited participants over eligible participants;3) Retention rate: the percentages of participants in both groups at the end of treatment and end of follow-up over the number of participants randomized;4) Completion rate: the percentage of participants who completed the treatment phase over the number of participants randomized.

Semi-structured interviews will be conducted to further explore the feasibility among the trial participants.

#### Efficacy outcomes

2.9.2

The efficacy of TQF for people with stage 2-4 DKD will be assessed on renal-related outcomes every 12 weeks.

The eGFR slope will be measured at the end of the treatment. eGFR slope is a validated surrogate endpoint for clinical trials to indicate kidney disease progression (33, 34). The Chronic Kidney Disease Epidemiology Collaboration (CKD-EPI) equation will be used to calculate eGFR (36).

Other efficacy outcomes will be measured from baseline to the end of treatment: changes in UACR, UPCR, serum creatinine, blood urea nitrogen, uric acid, HbA1c, fasting blood glucose (FBG), and blood lipids (cholesterol, triglycerides, low-density lipoprotein cholesterol, and high-density lipoprotein cholesterol). The laboratory equipment for all the laboratory outcomes will be standardized and follow a consistent operating procedure. Additionally, the changes in the score of the Dampness Syndrome Scale of Chinese medicine and the survival time of renal composite endpoint events will also be evaluated (35). The survival time is defined as starting from baseline to the occurrence of any of the below composite endpoints (37): receipt of a kidney transplant, initiation of maintenance dialysis, death from kidney failure, a sustained low eGFR, and a sustained percent decline in eGFR.

#### Safety outcomes

2.9.3

The blood samples will be collected and tested for safety every 12 weeks, including serum creatinine, potassium, phosphorus, calcium, alanine transaminase, aspartate transaminase, albumin, globulin, and full blood count (whole blood). Urine routine test, fecal routine, occult blood test, electrocardiograph, and urinary color Doppler ultrasound will be assessed at baseline and the end of treatment. Adverse events or severe adverse events will also be evaluated as safety outcomes.

### Safety considerations

2.10

An adverse event (AE) is any unfavorable and unintended sign (including an abnormal laboratory finding), symptom, or disease temporally associated with TQF or TQF placebo that may or may not have a causal relationship with TQF or TQF placebo (38). Abnormal laboratory test results are considered adverse events only if they induce clinical signs or symptoms. Participants record any AE immediately in the 30-day medication diary or contact the researchers when they happen. The researchers will record the AE in the Adverse Event Form by referring to the 30-day Medication Diary.

A serious adverse event (SAE) or experience or reaction is any untoward medical occurrence that involves the potential to result in death, is life-threatening, permanently incapacitating, or results in hospitalization (39). If the SAE occurs, the principal investigator can apply for emergency unblinding when it is essential for further management of the participants. The details of SAE will be recorded in the Serious Adverse Event Form by researchers and submitted to the ethics committee at GPHCM within 7 days of the first knowledge of the SAE. Participants are suggested to seek medical support from the nearest hospital’s emergency department as necessary.

A Data and Safety Monitoring Board (DSMB) has been established by external experts in pharmaceutical research, nephrology, statistics, and ethics. The DSMB will hold regular meetings every three months during the trial to provide advice on the overall study progress and safety data. One research assistant will prepare a summary of interim, unblinded, comparative data only for the DSMB members at the regular meetings. The DSMB will evaluate and decide whether to continue, modify, or terminate the trial. The researchers will report SAEs immediately to DSMB and take appropriate treatment measures if this occurs. This way, participants’ benefits can be safeguarded, and credible and valid results can be produced.

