### Study design

2.1

A mixed methods design has been adopted in this study, encompassing qualitative and quantitative components. The quantitative part is a two-center, parallel, add-on, randomized, double-blind, placebo-controlled pilot trial, followed by semi-structured interviews with trial participants. The study protocol has been registered with the Chinese Clinical Trial Registry (No. ChiCTR2200062786), one of the International Clinical Trial Registration Platforms of the World Health Organization.

The design of the pilot trial is in line with the Standard Protocol Items: Recommendations for Interventional Trials (SPIRIT) 2013 Statement (24) (**Supplementary File 1**) and Consolidated Standards of Reporting Trials (CONSORT) 2010 statement: extension to randomized pilot and feasibility trials (25), while the interview part will comply with the Consolidated Criteria for Reporting Qualitative Research (COREQ): A 32-Item Checklist for Interviews and Focus Groups (26).

Sixty participants will be enrolled in the trial for 62 weeks, consisting of two weeks of run-in, 48 weeks of treatment, and 12 weeks of follow-up. The SPIRIT schedule of enrolment, interventions, and assessments and the trial flow diagram are shown in **Table 1** and **Figure 1**, respectively.

**Table 1 T1:** SPIRIT schedule of enrolment, interventions, and assessments.

Study period		Screening	Enrolment	Allocation	Intervention				Follow-up
**Timepoint**		-t1	** *0* **	t1	t2	t3	t4	t5	t6
		-2 w	0 d	2 w	14 w	26 w	38 w	50 w	62 w
**Enrollment**	Initial screening	X							
	Informed consent		X						
	Eligibility screening		X						
	Run-in								
	Randomization & allocation			X					
**Interventions**	TQF plus usual care								
	Placebo plus usual care								
**Assessments: Research activities**	General information questionnaire		X						
	Physical examination		X	X	X	X	X	X	X
	Case report form		X	X	X	X	X	X	X
	A 30-day medication diary				X	X	X	X	
	Medication compliance check				X	X	X	X	
	Credibility of blinding							X	
**Assessments: Efficacy outcomes**	eGFR slope			X	X	X	X	X	X
	Urine protein/urine creatinine			X	X	X	X	X	X
	Urine albumin/urine creatinine			X	X	X	X	X	X
	SCr, BUN, UA, TCO2			X	X	X	X	X	X
	Hemoglobin A1c			X	X	X	X	X	X
	*Fasting blood glucose*			X	X	X	X	X	X
	TG, TC, LDL-C, HDL-C			X	X	X	X	X	X
	Composite renal endpoint events			X	X	X	X	X	X
	A score of the dampness syndrome scale of chinese medicine								
**Assessments: Safety outcomes**	ALT, AST, ALB, GLB			X	X	X	X	X	X

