The secondary outcome time to composite renal endpoint events will be analyzed by the Kaplan-Meier method. The log-rank test will be employed to compare time to composite outcomes between the two groups, followed by Cox proportional hazards regression to estimate hazard ratios with 95% CIs. Other continuous outcomes will be performed by Student’s *t*-test or Mann-Whitney U-test, while categorical variables will be examined using the *chi*-square test or Mann-Whitney U-test. The Cochran-Mantel-Haenszel test will be used for categorical variables, adjusting for center-related effects. Subgroup analysis will consider risk factors including but not limited to age, gender, hypertension, and proteinuria. Additionally, the Fisher exact test will be utilized to compare the incidence rates of adverse events and adverse drug reactions throughout the treatment duration.

An ITT analysis will be applied using the imputation method for missing data. We expect less than 20% of missing data points. The linear trend at point method will be used to replace missing values. The existing series will be regressed on an index variable scaled from 1 to n, and the missing values will be replaced with their predicted values. If the predicted values cannot be computed, the last observation carried forward (LOCF) method will be used. We will perform a sensitivity analysis without imputation to assess the robustness of our results.

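### The protocol gives two incompatible rules for when an abnormal laboratory result is an adverse event, and schedules no adverse-event check at the week-62 visit

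*Protocol article*

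**What the plan says.** Section 2.10 (Safety considerations) opens by defining an AE as "any unfavorable and unintended sign (including an abnormal laboratory finding), symptom, or disease temporally associated with TQF or TQF placebo", whether or not the product caused it. The next sentence reads "Abnormal laboratory test results are considered adverse events only if they induce clinical signs or symptoms".

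On how AEs reach the record, the same section states: "Participants record any AE immediately in the 30-day medication diary or contact the researchers when they happen". Researchers then complete the Adverse Event Form by reference to that diary. No end date for recording is given.

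Section 2.9.3 (Safety outcomes) states "The blood samples will be collected and tested for safety every 12 weeks". Its list includes creatinine, potassium, phosphorus, calcium, ALT, AST, albumin, globulin and the blood count, with AEs named as a further safety outcome.

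Table 1 places visits at weeks 2 (t1, allocation), 14, 26, 38, 50 and 62 (t6). The AEs/SAEs row is marked at weeks 14 to 50 and blank at week 62. The diary row has the same pattern: "A 30-day medication diary X X X X". Physical examination, the case report form and the safety blood tests are all marked at week 62.

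Section 2.14 (Statistical analysis) uses Fisher's exact test to "compare the incidence rates of adverse events and adverse drug reactions throughout the treatment duration".

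**The concern.** The definition of an AE decides what enters the AE count. Here two consecutive sentences give opposite answers for symptomless laboratory changes, which are the kind of change that 12-weekly blood tests exist to find. Two sites, or two investigators at one site, could each follow the protocol and classify the same result differently.

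The reporting route works in the same direction as the narrower rule. A participant can write a symptom in a diary, but cannot report a potassium or transaminase value they do not feel. No step in the document turns such a test result into an AE.

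Safety is a stated aim of the trial, and eligibility extends down to an eGFR of 15 mL/min/1.73m². The Introduction also shows how an AE count can be used: it reports that no AEs occurred in the earlier single-arm study and then draws a favourable safety conclusion. A count that leaves out symptomless laboratory changes could support the same conclusion whatever those tests showed.

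The second issue is the follow-up period. Participants attend at week 62, are examined and give blood for safety, but the schedule does not ask about AEs. The diary stops with treatment, so the usual recording route ends at the same time.

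**Working it through.** The protocol states no figure to reproduce here. The check sets the passages side by side and does the schedule arithmetic.

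**1. The two rules applied to the same result**

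| Laboratory result | First sentence of 2.10 | Second sentence of 2.10 |
|---|---|---|
| Abnormal, with signs or symptoms | AE | AE |
| Abnormal, no signs or symptoms | AE | Not an AE |

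The sentences disagree on the second row only, but they disagree completely there.

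**2. Where a symptomless abnormality ends up under the second sentence**

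- AE incidence compared by Fisher's exact test (2.14): not counted.
- Laboratory safety outcomes (2.9.3; Table 1, weeks 2 to 62): still measured and recorded.
- Data and Safety Monitoring Board (2.10): meets every three months and receives safety data.

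The loss is therefore confined to the AE count and to anything reported from it.

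**3. Scheduled AE coverage** (inputs from Section 2.1 and Table 1)

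- Trial length: 2 (run-in) + 48 (treatment) + 12 (follow-up) = 62 weeks, which agrees with the stated total.
- Post-randomisation time: 62 − 2 = 60 weeks.
- Time covered by scheduled AE assessments: 50 − 2 = 48 weeks; 48/60 = 80%.
- Time not covered: 62 − 50 = 12 weeks; 12/60 = 20%.
- Post-randomisation visits: weeks 14, 26, 38, 50 and 62, so 5. AEs/SAEs are marked at 4 and blank at 1.
- With week 62 marked: 5 of 5 visits and 60 of 60 weeks.

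**4. Size of the under-count**

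This would need the rate of symptomless laboratory abnormality in each arm. The document gives none, so no figure can be computed.

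**The case against.** **The second sentence may be a deliberate narrowing.** The first sentence is a general definition with a guideline reference, and the second could be this trial's working limit on it. That softens the charge of contradiction, but the text does not signal it, and the consequence is unchanged: symptomless changes leave the AE count.

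**Laboratory safety is not lost.** This stands, and it limits the point. A reader might infer that safety as a whole would be under-reported, or that the safety conclusion would rest on the AE count alone. The documents do not support that. The values are safety outcomes in their own right to week 62, the general provisions of 2.14 for continuous and categorical outcomes can cover them, and the monitoring board sees safety data. Predefined laboratory limits and shift tables are commonly left to an analysis plan, which is not shown, so their absence is no finding.

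**Follow-up AEs are not barred.** This also stands. A reader might infer that there would be no AE record after treatment. Section 2.10 sets no end date, participants may contact the researchers, and SAE reporting has no stated cut-off. What is missing is scheduled collection.

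**An on-treatment comparison is a legitimate choice.** Agreed. The window in 2.14 matches the AE row of Table 1 and is not an error. The week-62 visit simply offers information that the schedule does not collect.

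**Illustrative probabilities do not measure the defect.** One could assume a 5%, 10% or 20% rate of symptomless toxicity in 30 treated participants. The chance of at least one case, 1 − (1 − p)^30, is then 79%, 96% or 99.9%. One could contrast this with a report of 0/30, whose one-sided 95% upper bound is 1 − 0.05^(1/30) = 9.5%. But the rates are assumptions, a zero count would also need no other AE of any kind, and the protocol plans no such bound.

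**Conclusion.** The concern holds in a limited form. Section 2.10 gives incompatible rules for symptomless laboratory abnormalities. If the second sentence is followed, the AE incidence compared between arms omits them and is under-counted to the extent that they occur. The amount cannot be computed from the document, and the underlying laboratory values remain available.

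Separately, scheduled AE/SAE collection covers 48 of 60 post-randomisation weeks and 4 of 5 visits. The remaining 12 weeks (20%) depend on unsolicited contact and SAE reports, although the participant is seen and tested at week 62. This rests on reading the blank cell in Table 1 as intended, which the matching diary row and the analysis window in 2.14 both support.

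The wording needs correcting even in a 60-person pilot with feasibility as its primary outcome, because it is a stated rule that governs classification during conduct. The week-62 cell is a smaller gap.

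**What to change.** 1. **Section 2.10:** reconcile the two sentences by removing the symptom condition, so that an abnormal laboratory result the investigator judges clinically significant is recorded as an AE with or without signs or symptoms. Say that the researcher enters it from the laboratory report, since the diary cannot capture it. The judgement is made blind to allocation, as Section 2.7 already provides.
2. **Table 1:** mark AEs/SAEs at t6 (week 62).
3. **Section 2.14:** keep the on-treatment comparison and report AEs from weeks 50 to 62 by arm beside it. Section 2.8.3 offers TQF to the placebo group only after follow-up, so the arms stay distinct in that window.

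The article describes the trial as ongoing, so laboratory results already on file should be reviewed under the revised rule before unblinding.

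The cost is protocol wording, one table cell, a short extra safety summary and a somewhat higher reported AE count. No additional visit or blood test is needed. What is given up is the smaller AE listing that the symptom condition would produce.

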	Serum potassium/phosphorus/calcium			X	X	X	X	X	X
	Blood/urine routine test			X	X	X	X	X	X
	Fecal routine and occult blood test			X	X	X	X	X	X
	Electrocardiograph			X				X	
	Urinary color doppler ultrasound			X				X	
	AEs/SAEs				X	X	X	X	
**Qualitative study**	Semi-structured interviews								X

TQF, Tangshen Qushi Formula; GFR, glomerular filtration rate; SCr, serum creatinine; BUN, blood urea nitrogen; UA, uric acid; TCO2, total carbon dioxide; TG, triglyceride; TC, total cholesterol; LDL-C, low-density lipoprotein cholesterol; HDL-C, high-density lipoprotein cholesterol; ALT, alanine transaminase; AST, aspartate transaminase; ALB, albumin; GLB, globulin; AE, adverse event; SAE, serious adverse event; -t_1_: time point before day 0, t_1_: time point 1, t_2_: time point 2, and so on.

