### Ethics and dissemination

2.3

Ethics approval has been obtained from the ethics committee of Guangdong Provincial Hospital of Chinese Medicine (GPHCM) (No. YF2022-152-01) and Guangxi Hospital of Chinese Medicine (GXHCM) (No. LS2022-021-02) (**Supplementary File 3**). The ethics approval is also filed with the RMIT ethics committee (No. 2022-24963-18150). Written informed consent will be obtained from the eligible participants before the baseline assessment and data collection. This study will follow the *Declaration of Helsinki, Guideline for Good Clinical Practice ICH E6 (R2) ICH Consensus Guideline* and *Measures for the Ethical Review of Biomedical Research Involving Humans (2016, in Chinese)*. Medical records and biological samples may be used again in future similar studies. In this case, ethics approval will be obtained before the release of the materials. The results from this study will be published in peer-reviewed medical journals, Ph.D. thesis, and/or scientific conferences. However, any information obtained from this study that can identify an individual will remain confidential and only be used for this study. A one-page summary of the results will be provided to study participants.

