### Withdrawal and termination

2.11

Participants may voluntarily withdraw from the study for any reason at any time. Participants will be considered withdrawn if they state an intention to withdraw, reach composite renal endpoint events, or become lost to follow-up for any other reason. When withdrawal occurs, the researcher must determine the primary reason for premature withdrawal from the study and record this information on the Case Report Form (CRF). The research team and study doctor may remove a participant from further participation in this study if (1) staying in the study would be unsafe or harmful to the participant; (2) the participant needs treatment that is not allowed in this study; (3) participant fails to follow instructions; (4) participant becomes pregnant. This study may be stopped for several reasons, including unacceptable side effects, the intervention being shown to have no effect, or being effective with no need for further investigation.

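### The SAE definition printed in 2.10 does not cover events that prolong an existing hospital stay or incapacity not yet known to be permanent, so these can miss expedited reporting; 2.9.3 also says 'severe' where 2.10 and Table 1 say 'serious'

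*Protocol article*

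**What the plan says.** Section 2.10 (Safety considerations) prints the SAE definition as a list of four limbs: "any untoward medical occurrence that involves the potential to result in death, is life-threatening, permanently incapacitating, or results in hospitalization". It has no clause for prolonged stays and none for other medically important events.

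Two duties hang on the term. SAE details are to be "submitted to the ethics committee at GPHCM within 7 days of the first knowledge of the SAE". For the monitoring board, "The researchers will report SAEs immediately to DSMB and take appropriate treatment measures if this occurs". The same section lets the principal investigator apply for emergency unblinding when an SAE occurs.

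Other events are handled more slowly. Section 2.10 defines an adverse event broadly and has it entered on an Adverse Event Form. It also states: "The DSMB will hold regular meetings every three months during the trial to provide advice on the overall study progress and safety data".

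Section 2.9.3 (Safety outcomes) uses a different word: "Adverse events or severe adverse events will also be evaluated as safety outcomes". The footnote to Table 1 expands the abbreviations as "AE, adverse event; SAE, serious adverse event".

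On pregnancy, 2.4.2 excludes pregnant or breastfeeding women at entry, and 2.11 gives "participant becomes pregnant" as a ground for removal. Section 2.3 says the study will follow ICH E6 (R2) but does not reproduce its SAE criteria.

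**The concern.** A definition that triggers urgent reporting has to be usable on the day the event becomes known. Two of the four limbs work poorly on that test.

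- **Hospitalization.** The limb asks whether the event led to the admission. A complication that arises during an admission and extends it did not lead to that admission.
- **Incapacity.** The limb asks for permanence. Permanence is usually established only after a period of observation, whereas the reports are due at once and within 7 days.

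At stake is the speed with which some harms reach the people charged with protecting participants. The DSMB decides whether the trial continues, changes or stops, and the ethics committee has no other stated source of event reports. The population has diabetes and kidney disease with eGFR down to 15 mL/min/1.73m², so hospital stays during the trial are plausible.

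The wording of 2.9.3 adds a smaller problem. Severity describes intensity, while seriousness, as 2.10 uses it, describes consequence. An outcome labelled 'severe' is not the quantity that the Serious Adverse Event Form collects.

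**Working it through.** No figure in the article attaches to this point, so there is nothing to recompute. The check sets the sections against each other.

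**1. Which events meet the printed definition?**

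| Event | Limb that could apply | SAE as printed? |
|---|---|---|
| Event that causes an admission | Results in hospitalization | Yes |
| Complication that extends an admission already under way | None, unless life-threatening, potentially fatal or permanently incapacitating | No, read literally |
| Significant incapacity managed without admission, permanence unknown | None, unless life-threatening or potentially fatal | Not when first known |
| Incapacity shown to be permanent | Permanently incapacitating | Yes, but only once that is known |

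**2. What reporting follows?**

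| Route | SAE | Event recorded only as an AE |
|---|---|---|
| DSMB | Immediately | At the three-monthly review of safety data |
| Ethics committee at the lead hospital | Within 7 days of first knowledge | None stated |

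For the DSMB, an event in the second or third row of the first table therefore moves from immediate notice to a delay of up to about three months. For the ethics committee it moves from 7 days to no stated report.

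The 7-day clock might be read as starting only when the event is recognised as serious. An incapacity would then be reported on time by the rule, but only after its permanence had been settled. The rule is met and the early notice is still lost.

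**3. Does 'severe' in 2.9.3 remove any event?** No. The sentence lists adverse events of every kind next to severe ones. Table 1 schedules AEs/SAEs with SAE expanded as serious, and the reporting duties in 2.10 use SAE. The Fisher exact comparison in 2.14 concerns adverse events and adverse drug reactions, so it is unaffected too. What remains is an undefined term that does not match the one collected.

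**4. Pregnancy.** Entry is barred (2.4.2) and pregnancy during the trial is foreseen (2.11), but the article states no reporting of its outcome. This gap is narrow.

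**The case against.** The strongest reply is that this is a condensed article. The full protocol and the Serious Adverse Event Form are not shown and may carry complete criteria, and 2.3 commits the study to ICH E6 (R2), which could govern where the summary is short. This has weight against a charge of mere omission. It has less against a definition printed as a closed list and tied to reporting deadlines. If the form is fuller, it disagrees with 2.10 and the two still need reconciling. Because the standard's list is not reproduced, the case here rests on how the printed rule works and not on a proven departure from the standard.

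Other parts of the reply stand:

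- A reader might infer that the omitted events would never reach the DSMB. The documents do not support that: they meet the broad AE definition and fall within the safety data reviewed every three months. Only immediate notice is lost.
- A reader might infer that 2.9.3 counts severe events in place of serious ones. It does not, since it counts all adverse events.
- A reader might try to estimate the number of admissions affected, or treat each missed SAE as moving an arm's proportion by 1/30 = 3.3 percentage points. The article gives no admission rate. A complication in a participant already counted as having an SAE moves no proportion.
- The prolonged-stay gap affects only people already in hospital. The limb on potential to cause death is broad enough to catch some grave events.
- On unblinding, the text permits an application when an SAE occurs but does not say that other events are barred.

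**Conclusion.** The point holds in a limited form. Applied as printed, the definition in 2.10 leaves events that prolong an existing stay, and significant incapacity not yet known to be permanent, outside expedited reporting. For those events the DSMB would learn at its next quarterly review instead of immediately, and the ethics committee has no stated route. The word 'severe' in 2.9.3 is a mismatch of terms that loses no event.

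The size is a loss of timeliness for an unknown, probably small, number of events. The documents do not support a claim that the trial's safety conclusion would change. The verdict assumes that site staff apply 2.10 as written and that adverse events recorded on the form enter the DSMB's quarterly safety data. The pregnancy element is minor and belongs with the alignment to the cited standard.

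**What to change.** In 2.10, extend the definition to events that require or prolong hospitalization and to persistent or significant incapacity, so that permanence need not be known before reporting. Check the whole list against the ICH E6 (R2) standard named in 2.3, including how pregnancy outcomes are reported, and make the Serious Adverse Event Form agree with it. In 2.9.3, replace 'severe' with 'serious' so that the stated outcome matches Table 1 and 2.10.

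The cost is wording changes to the protocol, and to the form if it differs, and possibly a few more expedited reports. No change to the design, sample size or planned analyses is needed.
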